### Analysis of effectiveness

The principle of intention-to-treat will be used for analysis, and each of the outcome parameters will be compared between the intervention and the control groups. A simple test of proportions will be used to test the primary hypothesis. The secondary hypotheses will be tested in two probit regressions: one for user characteristics and one for appointment type characteristics. Both models will have attendance as the dependent variable and a randomization group dummy and user/appointment type characteristics as covariates along with interaction terms for the randomization group dummy and the covariates. The interpretation of the interaction terms will then be the effect modification of the covariates, which is the same as a differentiated effect of fines on different users/types of appointments. A significance level of 0.05 will be used for all analyses.

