## Background

Recent hospital episode statistics from the United Kingdom show that approximately 20 % of scheduled outpatient appointments are nonattended [1]. While hospital and user cancellations each account for almost one third of the nonattended appointments, 7 % of nonattended appointments remain unaccounted for. Seven percent nonattendance is estimated to represent a cost to the healthcare system of around £790 million per year in the United Kingdom [2].

Outpatient nonattendance refers to the phenomenon of users who have an appointment but do not show up at the specified date, time, and location without giving notice. In addition to affecting the efficiency of production and thereby increasing the total costs of care, nonattendance might also delay access to care for users on waiting lists. Moreover, nonattendance has been suggested to have a detrimental effect on health outcomes [3, 4], an effect that is unevenly distributed across disease and socioeconomic groups [5, 6].

Stubbs et al. conducted a systematic literature review to assess the efficacy of various reminder interventions for reducing outpatient nonattendance such as telephone, mail, text/short message service, e-mail reminders, and open-access scheduling [7]. They found that almost all of the assessed interventions moderately reduced nonattendance. However, much of this evidence was based on observational studies, and most studies did not control for socioeconomic status and other relevant factors such as age, sex, waiting time, and health-problem characteristics. The recognition of a need for further high-quality studies has been confirmed by similar systematic reviews [8–10].

Another means for reducing outpatient nonattendance, for which there appears to be only vague empirical evidence, is to penalize nonattendance by a fine. According to neoclassical economic theory, user behavior can be influenced by financial incentives. The introduction of a fine for nonattendance will create a stronger incentive for users to appear at their scheduled appointments [11]. This has been demonstrated in two earlier observational studies where the introduction of fines led to a 14 % reduction and a 54 % reduction in nonattendance [12, 13]. These studies, however, only represent before-and-after scenarios, do not consider the likely influence of exogenous factors, and have limited sample sizes. Furthermore, the external validity is questionable due to the 20-year time lag.

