### Sample size

Based on department statistics, a nonattendance rate of 4.8 % and a volume of 6,500 eligible appointments during a time window of 7 months are assumed. This time window was adopted to balance of arguments concerning effect size and stability in the study, which are exerted for restructuring and cost cutting after the 7 months. A minimum reduction of 1.58 % (from 4.8 % to 3.22 %) was found using a chi-squared test and a 90 % power level. The randomization ratio is 1:1, which indicates that 3,250 users are required in each arm. The power to detect similar impacts on the secondary outcome parameters of cancellations will be higher due to higher baseline proportions. The power to detect the impact on sociodemographics will depend on the scaling and the relevant level of relative risk reduction [19].

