### Measures of effectiveness

The primary outcome measure is the proportion of appointments that are attended. The secondary outcomes, which are covariates, include the proportions of sociodemographics (age, sex, income, education, distance to hospital, travel time, and waiting times) and health-problem characteristics (anatomy, type of appointment and treatment costs). All parameters except for sociodemographics are automatically extracted from the electronic patient journal system into a trial registry and administratively registered in electronic trial registries. Data on sociodemographics are extracted from various, individual user-level, national registries administered by Statistics Denmark.

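### The unadjusted primary test is valid but leaves planned baseline covariates unused; a prespecified covariate-standardised risk difference would be a small gain in precision at almost no cost

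*Protocol article*

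**What the plan says.** All quotes are from the protocol article.

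- **Primary analysis** (Analysis of effectiveness): "A simple test of proportions will be used to test the primary hypothesis", under intention-to-treat. The same section adds: "A significance level of 0.05 will be used for all analyses". Sidedness is not stated.
- **Secondary analysis** (same section): two probit models of attendance contain arm, user or appointment characteristics, and their interactions with arm. These serve the secondary hypotheses only.
- **Covariates** (Measures of effectiveness): the list comprises "the proportions of sociodemographics (age, sex, income, education, distance to hospital, travel time, and waiting times) and health-problem characteristics", the latter being anatomy, type of appointment and treatment costs. On source: "All parameters except for sociodemographics are automatically extracted from the electronic patient journal system". Sociodemographics come from national registries held by Statistics Denmark.
- **Sample size**: the planning inputs are "a nonattendance rate of 4.8 % and a volume of 6,500 eligible appointments during a time window of 7 months are assumed". On the detectable effect the section states: "A minimum reduction of 1.58 % (from 4.8 % to 3.22 %) was found using a chi-squared test and a 90 % power level". Allocation is equal, with 3,250 per arm.
- **Background**: earlier evidence is criticised because "most studies did not control for socioeconomic status and other relevant factors such as age, sex, waiting time, and health-problem characteristics".
- **Cost-effectiveness**: the effect measure is taken over from the effectiveness analysis.

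**The concern.** The trial's window and volume were set in advance, and the article reports that the trial closed on 1 December 2015. More precision can therefore come only from the analysis. The article itself regards age, sex, waiting time and type of health problem as relevant to nonattendance, plans to obtain them, and plans to regress attendance on them. Only the primary comparison does without them.

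A risk difference standardised over baseline covariates targets the same difference in proportions. With a robust standard error it remains valid under randomisation even if the working model is wrong, and in a sample of this size it should lose essentially no precision. At stake is the width of the interval around the main answer. The effect term of the cost-effectiveness ratio is affected as well, because it is taken from the same analysis.

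**Working it through.** **1. Reproduce the plan's figure.** Inputs from the Sample size section: p1 = 0.048, p2 = 0.0322, 3,250 per arm, 90 % power, chi-squared test. Alpha is 0.05 from Analysis of effectiveness. I take it as two-sided, because a one-sided test would need only 2,640 per arm.

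Mean proportion p̄ = (0.048 + 0.0322)/2 = 0.0401.

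n per arm = [1.960·√(2p̄(1−p̄)) + 1.282·√(p1(1−p1) + p2(1−p2))]² / (p1−p2)²

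= [1.960·0.27746 + 1.282·0.27723]² / 0.0158² ≈ 3,239.

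The plan states 3,250, at which power is 90.1 %. The figure reproduces.

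**2. Unadjusted precision.** SE = √[(0.048·0.952 + 0.0322·0.9678)/3,250] = 0.004863. The 95 % half-width is 1.96 × 0.004863 = 0.953 percentage points.

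**3. Effect of adjustment.** The variance of the adjusted difference is approximately (1 − R²) times the unadjusted variance, where R² is the share of outcome variance explained by the baseline covariates. Hence half-width = 0.953·√(1 − R²) and effective n per arm = 3,250/(1 − R²).

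**4. Range for R² (an assumption).** The article gives no measure of prognostic strength.

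- Low end: one binary predictor, present in 25 % of users, that halves nonattendance. With an overall rate of 4 %, the two rates are 0.04/0.875 = 0.0457 and 0.0229. Then R² = 0.25·0.75·(0.0457 − 0.0229)²/(0.04·0.96) ≈ 0.003.
- Upper part: a normally distributed risk score on the logit scale at 4.8 % prevalence. A standard deviation of 0.6, 0.75 or 1.0 gives an AUC of about 0.66, 0.70 or 0.75 and an R² of about 0.018, 0.030 or 0.056.

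**5. Results at 4.8 % versus 3.22 %, 3,250 per arm.**

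| Assumed R² | Power | 95 % half-width (points) | Equivalent extra users, both arms |
|---|---|---|---|
| 0 (as planned) | 90.1 % | 0.953 | 0 |
| 0.003 | 90.2 % | 0.952 | about 20 |
| 0.018 | 90.6 % | 0.945 | about 119 |
| 0.030 | 90.9 % | 0.939 | about 201 |
| 0.056 | 91.7 % | 0.926 | about 386 |

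**6. Break-even for missing covariates.** If users without linked covariates were dropped, losing a fraction of users equal to R² would cancel the gain: 6,500 × 0.003 ≈ 20, 6,500 × 0.018 = 117, 6,500 × 0.030 = 195, 6,500 × 0.056 = 364. The gain survives only if nobody is excluded for a missing covariate.

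**7. Cost-effectiveness ratio.** Its precision also depends on the variability of costs, which the article does not give. The gain there cannot be computed.

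**The case against.** The strongest objection is that nothing is broken. Randomisation is 1:1 at user level with one appointment per user, so the simple test is unbiased and agrees with a sample size that reproduces. This stands, and it limits the point to an efficiency improvement.

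Four further objections stand in part and narrow the fix:

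- **Availability.** A reader might infer that the trial already holds prognostic data for every booking. The article does not support this. Age, sex, travel time and waiting times are classed as sociodemographics, which require registry linkage. Completeness rests only on the statement that missing data are not relevant for register data.
- **Timing.** Not every listed variable is clearly a baseline variable. The Setting section says users can reschedule, so waiting time measured to the final date could be affected by the fine letter. Treatment costs are not shown to be fixed at booking.
- **Relevance.** A reader might take the Background's criticism of earlier studies as proof of a worthwhile gain. That criticism is aimed at largely observational evidence, where the issue is mainly confounding, which randomisation handles. It says nothing about how much precision this trial would gain.
- **Late change.** Altering the primary analysis after closure can look post hoc. The article says the researchers remain blind throughout data analysis, so a dated change made before allocation is revealed answers this.

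**Conclusion.** The point holds as a minor improvement. The planned test is valid; the plan simply forgoes a little precision that its own data could supply. Over an assumed R² of 0.003 to 0.056, power rises by about 0.1 to 1.6 percentage points from 90.1 %, and the interval narrows by about 0.2 % to 2.8 %.

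These figures assume a two-sided 5 % test, the plan's own 4.8 % and 3.22 %, variance scaling by 1 − R², and no user excluded for a missing covariate. A reader might infer that the primary result is biased or underpowered, or that the cost-effectiveness ratio loses a known amount of precision. The document supports none of these: the test is unbiased, power is 90.1 % at the stated effect, and the loss on the ratio cannot be quantified.

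**What to change.** Before unblinding, prespecify the following in a dated addition to the analysis plan:

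1. **Primary estimate:** a covariate-standardised risk difference by g-computation from a main-effects logistic or probit model, with a robust standard error.
2. **Covariates:** only variables fixed at randomisation, namely age, sex, appointment type, anatomy and travel time. Include waiting time only if it is defined from the originally booked date. Exclude treatment costs.
3. **Missing covariates:** keep all randomised users, with a missing indicator or simple imputation for any covariate that does not link.
4. **Sensitivity analysis:** report the simple test of proportions alongside.
5. **Cost-effectiveness:** the adjusted difference may be used as the effect term, without claiming a stated gain there.

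The cost is a few lines of text and one extra model, using data already planned for extraction. No further enrolment is needed.

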In Denmark, the introduction of fines for nonattendance in hospital outpatient clinics has been debated for years [14]. In 2005, a collaborative agreement between the Danish Regions and the Danish Medical Association opened the opportunity for privately practicing specialists to issue nonattendance fines of Danish kroner (DKK) 250 for consultations and DKK 500 for surgical procedures (1 EUR = 7.45 DKK) [15]. Overall, the expected benefits were related to a better use of resources, whereas concerns were expressed about the detrimental effect on equal access for equal needs, as the fines would impact the most vulnerable users most strongly. Moreover, the use of fines was seen as a break with the fundamental value of free and equal access to healthcare and a potential threat to the patient-health professional relationship, which ideally should be independent of financial interests [14].

Although 10 years have passed since the regulatory context cleared the way for fines in the Danish healthcare system for privately practicing specialists, no systematic evidence on the resulting practice, efficacy, or effect appears to have been reported. Therefore, the Danish Regions have decided that the effect of using fines to moderate nonattendance at somatic, hospital-based, outpatient clinics in Denmark should be scientifically investigated [16]. This trial is a result of that decision and, in accordance, the aim of this trial is to investigate the effect of fines on nonattendance in a hospital-based outpatient clinic. The primary hypothesis is that the risk of fines will incentivize healthcare-service users to attend appointments more often than if no risk of fines is associated with nonattendance of a planned appointment. A secondary hypothesis is that the pattern of attendance will be affected by the risk of fines in terms of who attends (user characteristics) and what type of appointment is being attended (appointment characteristics). The rationale for the second hypothesis is to address the political focus on preserving equal access to healthcare and on variation in provider efficiency. Finally, a third hypothesis is that the use of fines in routine practice will be cost effective.

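### The interaction terms of the probit models are equated with a differentiated effect of fines without naming a scale; they are not the difference in the effect on the proportion of nonattendance

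*Protocol article*

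**What the plan says.** The Background section of the protocol article sets a secondary hypothesis that "the pattern of attendance will be affected by the risk of fines in terms of who attends", and likewise in terms of the type of appointment attended. It gives equal access to healthcare as a reason for asking.

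Under Analysis of effectiveness, this hypothesis is tested in two probit regressions of attendance, one with user characteristics and one with appointment characteristics. Each contains a randomization dummy, the covariates and their interactions with the dummy. The reading of the result is fixed in advance: "The interpretation of the interaction terms will then be the effect modification of the covariates, which is the same as a differentiated effect" of fines across users or appointment types. The section adds that "A significance level of 0.05 will be used for all analyses". It mentions no scale, predicted probability or marginal effect.

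The rest of the plan works with proportions. Under Measures of effectiveness, "The primary outcome measure is the proportion of appointments that are attended". The primary test is a test of proportions. The sample size is a fall in nonattendance from 4.8 % to 3.22 %. The cost-effectiveness ratio is the extra cost per additional nonattendance prevented. The Discussion plans weights to predict the effect in other user populations.

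**The concern.** In a probit model the arm coefficient is a shift on the normal index, and the interaction coefficient is the difference between two such shifts. The same shift changes a probability by more when the starting probability is nearer to one half. With nonattendance near 5 %, the link is strongly curved, so groups that start at different rates can have equal index shifts and quite different changes in nonattendance, or the reverse.

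Unequal baselines are plausible in this setting. Under Setting, SMS reminders are available only for follow-up appointments or for users who have attended before, so nonattendance may differ by appointment type. The Background treats socioeconomic status, age, sex and waiting time as factors that nonattendance studies should control for.

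At stake is the trial's answer on who is affected by fines and by how much, which is meant to inform national policy. Predicting the effect in other populations also needs subgroup effects on the proportion scale, and the coefficient does not give these directly.

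**Working it through.** **Inputs from the protocol (Sample size; Analysis of effectiveness).** The plan assumes "a nonattendance rate of 4.8 % and a volume of 6,500 eligible appointments", a reduction of 1.58 percentage points to 3.22 %, which "was found using a chi-squared test and a 90 % power level", and 3,250 users per arm. The significance level is 0.05, taken here as two-sided.

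**The plan's own figure.** For two proportions with pooled variance under the null and no continuity correction, with p̄ = (0.048 + 0.0322)/2 = 0.0401:

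n = [1.960·√(2p̄(1−p̄)) + 1.282·√(p₁(1−p₁) + p₂(1−p₂))]² / (p₁−p₂)² = 3,239 per arm.

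This reproduces 3,250, and power at 3,250 per arm is 90.1 %. The design rates are therefore sound anchors. The protocol states no figure for the interaction tests.

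**Assumptions.** Subgroup rates are not in the documents. Control-arm rates of 3 % for a low-risk group and 6.6 % to 10 % for a high-risk group are assumed below.

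**Formulas.** The shift in group g is s_g = z(p_fine) − z(p_control), where z is the inverse normal distribution function. With attendance as the dependent variable, the interaction coefficient (high-risk minus low-risk) is −(s_high − s_low). The contrast on the proportion scale is the reduction in the high-risk group minus the reduction in the low-risk group.

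**(a) Coefficient exactly zero.** The design shift is z(0.0322) − z(0.048) = −1.849 + 1.665 = −0.185. Apply it in every group:

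| Control rate | Rate with fine | Reduction (points) |
|---|---|---|
| 3 % | 1.94 % | 1.06 |
| 4.8 % | 3.22 % | 1.58 |
| 8 % | 5.59 % | 2.41 |
| 10 % | 7.13 % | 2.87 |

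Against the 3 % group, the reduction is 2.41/1.06 = 2.3 times as large at 8 % and 2.87/1.06 = 2.7 times as large at 10 %.

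**(b) Equal reductions of 1.58 points.** 3 % to 1.42 % is a shift of −0.311. 6.6 % to 5.02 % is a shift of −0.137. The coefficient is −(−0.137 + 0.311) = −0.174, although the reductions are identical.

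Take two equal groups (1,625 users per cell) and the approximation SE² = Σ p(1−p)/(n·φ(z(p))²), where φ is the normal density. This gives SE = 0.125, and a two-sided 5 % Wald test of the coefficient rejects about 29 % of the time.

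Conversely, with the same baselines, a coefficient of zero and an overall fall from 4.8 % to 3.22 %, the reductions are 1.07 and 2.09 points, a contrast of 1.02 points. The coefficient test then rejects 5 % of the time.

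**(c) Opposite sign.**
- 10 % to 7.5 % is 2.5 points, shift −0.158. 3 % to 1.8 % is 1.2 points, shift −0.216. The contrast is +1.3 points and the coefficient is −0.058. The risk ratios are 0.75 and 0.60.
- 6.6 % to 4.84 % is 1.76 points, shift −0.154. 3 % to 1.6 % is 1.40 points, shift −0.264. The contrast is +0.36 points and the coefficient is −0.109. The risk ratios are 0.73 and 0.53. Mixed 50/50, these rates average exactly 4.8 % and 3.22 %.

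With equal groups, the coefficient test is significant about 8 % of the time in the first case (SE 0.116) and about 15 % in the second (SE 0.123).

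**The case against.** The strongest reply is that effect modification always depends on scale and that the probit index is a legitimate scale. The sentence can be read as explaining a technical term in plain language and as incomplete rather than false. This stands as a defence of the model. It does not rescue an unqualified equation in a plan whose other quantities are proportions.

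A reader might infer that the coefficient would point to the wrong group. The documents do not support that. In the opposite-sign examples the coefficient agrees with the risk ratio, so two scales disagree and neither is an error. Such a reversal would also seldom reach significance.

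A reader might also infer that a null interaction will be reported as equal access. The protocol nowhere says so.

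The sizes rest on assumed subgroup rates, since the protocol gives only an overall rate and monthly clinic rates of 3 % to 6 % (Table 1). That stands.

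Finally, marginal effects could be left to a fuller plan. That would answer a complaint of omission, but here the article itself fixes the interpretation.

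**Conclusion.** The point holds as a misstatement about interpretation. Where baseline nonattendance differs between groups, the probit interaction coefficient is not the difference in the fine's effect on the proportion of nonattendance, and the protocol should not call it the differentiated effect without naming a scale. Under the assumed baselines, a zero coefficient can hide a 2.3- to 2.7-fold difference in absolute reduction, and equal absolute reductions can produce a coefficient of about 0.17 in absolute value.

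The size depends on how far baselines differ, and the discrepancy is nil if they are equal. The choice of probit is not at fault. The primary test of proportions and the sample size are unaffected; only the secondary hypotheses and what is built on them are touched.

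**What to change.** Keep both probit models. Replace the equating sentence with a statement that the interaction coefficients are contrasts on the latent index. Base the conclusion on differentiated effects on the average marginal effect of the fine, that is, the risk difference in nonattendance, at each level of each characteristic and on the difference between levels. Give 95 % confidence intervals by the delta method or bootstrap.

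A linear probability model should not be presented as interchangeable with this. It gives the same risk differences only when saturated, and age, income, distance, travel time and waiting times may enter as continuous covariates.

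The cost is one post-estimation step on models already planned, a change of wording and no new data. Precision will be limited. In the equal-groups example with baselines of 3 % and 6.6 %, a true contrast of 1.02 points has a standard error of about 0.97 points and would be detected about 18 % of the time. The intervals should therefore be reported and read as they stand, without treating a non-significant contrast as evidence of equal effects.

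### The secondary hypotheses rest on at least ten arm-by-covariate interactions at an unadjusted 0.05 with no joint test stated; read singly, the seven user terms carry about a 23-30 % chance of a false differential effect

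*Protocol article*

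**What the plan says.** The Background section of the protocol article sets out the hypothesis: "A secondary hypothesis is that the pattern of attendance will be affected by the risk of fines in terms of who attends (user characteristics", together with the type of appointment attended. It gives two reasons for asking: equal access to care, and variation in provider efficiency. The hypothesis is called secondary, not exploratory.

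The section Analysis of effectiveness gives the method: "The secondary hypotheses will be tested in two probit regressions: one for user characteristics and one for appointment type characteristics". Each model has attendance as the outcome and contains the arm, the characteristics and their products, that is "along with interaction terms for the randomization group dummy and the covariates". On reading the results it says: "The interpretation of the interaction terms will then be the effect modification of the covariates". The section closes with "A significance level of 0.05 will be used for all analyses".

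The section Measures of effectiveness lists the covariates. One group is "sociodemographics (age, sex, income, education, distance to hospital, travel time, and waiting times", seven items. The other is "health-problem characteristics (anatomy, type of appointment and treatment costs", three items. No section mentions a joint test of the interactions, an order of testing, a multiplicity adjustment, or exploratory status for single terms.

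**The concern.** Each model asks one question: does the effect of the fine differ across users, and does it differ across appointment types? The text supplies several coefficients per question and one significance level for everything. An analyst who follows it would naturally look at each interaction p-value against 0.05 and report any that pass as a differential effect. The more terms there are, the more likely that one passes by chance.

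Equal access is the main argument of those who oppose fines (Discussion), and the results are meant to inform national decisions. A chance finding that, say, one income or education group responds differently could weigh in that debate. True interactions will also be hard to see. At the planning rates the trial expects about 3,250 x 0.048 + 3,250 x 0.0322 = 156 + 105 = 261 nonattendances in all, and the Sample size section quantifies no power for the sociodemographic analysis. An isolated significant term would be weak evidence.

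**Working it through.** **Inputs.** The level is 0.05 (Analysis of effectiveness). There are 7 user and 3 health-problem characteristics (Measures of effectiveness), matched here to the user model and the appointment model. With one term per characteristic, k = 7, 3 and 10 over both. Coding education, anatomy or appointment type as several categories would add terms; the coding is not given.

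**The plan's own figure.** The document gives no family-wise error rate. Its sample size shows which 0.05 is meant. With p1 = 0.048, p2 = 0.0322, mean 0.0401 and 90 % power:

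n = [1.960 x sqrt(2 x 0.0401 x 0.9599) + 1.2816 x sqrt(0.048 x 0.952 + 0.0322 x 0.9678)]² / 0.0158² = 3,239 per arm.

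The protocol states 3,250, which gives 90.1 % power. A one-sided test would need 2,640. So 0.05 is two-sided, and |z| > 1.96 is used below.

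**Independent tests.** The chance of at least one false positive is 1 - 0.95^k.

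- k = 7: 1 - 0.698 = 30.2 %
- k = 3: 1 - 0.857 = 14.3 %
- k = 10: 1 - 0.599 = 40.1 %
- k = 15, if categories add terms: 53.7 %

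**Correlated tests.** The document gives no correlation, so this is an assumption. With equal pairwise correlation r between normal test statistics, the chance is 1 - E{[Φ((1.96 - √r·U)/√(1-r)) - Φ((-1.96 - √r·U)/√(1-r))]^k}, with U standard normal.

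| r | user, k = 7 | appointment, k = 3 | both, k = 10 |
|---|---|---|---|
| 0 | 30 % | 14 % | 40 % |
| 0.3 | 27 % | 14 % | 35 % |
| 0.5 | 23 % | 13 % | 29 % |
| 0.8 | 15 % | 10 % | 17 % |

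**Check on the models themselves.** The two probit models were simulated with n = 6,500, nonattendance of 4.8 % and 3.22 %, continuous covariates and no true interaction (1,500 runs).

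| | any user term | any appointment term | either |
|---|---|---|---|
| covariates uncorrelated | 30.9 % | 13.9 % | 40.0 % |
| one pair (as for distance and travel time) correlated 0.9 | 26.4 % | 12.7 % | 35.2 % |

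The Monte Carlo standard error is at most sqrt(0.4 x 0.6 / 1,500) = 1.3 points. In the same runs a joint Wald test of all interactions was significant in 4.1 % (user model, both settings) and in 4.7 % and 4.0 % (appointment model). With two independent joint tests at 0.05, the chance of either being falsely significant is 1 - 0.95² = 9.75 %.

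**Price of the joint test.** Suppose one user characteristic alone modifies the effect and its single-term test has 80 % power. The noncentrality is then about (1.960 + 0.842)² = 7.85. The joint test on 7 degrees of freedom has critical value 14.07 at 0.05, and P(χ²₇(7.85) > 14.07) is about 49 %. At 0.025 the critical value is 16.01 and the power about 38 %.

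**The case against.** The strongest reply is that the text does not say the terms are tested one by one. A single joint test per model at 0.05 is compatible with every sentence in Analysis of effectiveness. Coding, choice of test statistic and secondary multiplicity are often left to an analysis plan, and none is shown here. This stands in part: single-term reading is an inference, and the figures above are conditional on it. It does not remove the point. The protocol is not silent on error control. It names the models, the terms and how they are to be read, and then sets 0.05 for everything. Following that text as it stands invites the inflation.

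A second reply is that user and appointment characteristics are separate questions in separate models, serving two stated purposes. That stands. A reader might infer that the equal-access conclusion carries the 29-40 % risk of all ten terms. The document does not support this, because three of the ten describe the appointment; the figure for users is 23-30 %. For the same reason, adjustment across the two models is not required.

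A third reply is that a joint test can miss real inequity carried by one characteristic. That also stands. The fall from 80 % to about 49 %, or 38 % if the level were halved as well, is a real loss. It argues against forbidding any discussion of a single term when the joint test fails.

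A reader might also infer that chance interactions would pass into the weights planned in the Discussion for predicting effects in other populations. The text does not say those weights depend on which interactions are significant, so this does not follow.

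**Conclusion.** The point holds as a weakness in a stated rule, limited to the secondary hypotheses. With one term per characteristic, a uniform fine effect and single-term reading, the chance of at least one false interaction is about 23-30 % for the user model, 13-14 % for the appointment model and 29-40 % over both. For the equal-access question that is roughly five to six times 5 %.

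The ranges rest on an assumed correlation between tests of 0 to 0.5. At 0.8 they fall to about 15 % for the user model and 17 % over both, still three times 5 % or more. Categorical coding would push them up. The primary comparison of proportions is a single named test, and its error rate is untouched. It would be wrong to read this as a threat to the main result.

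**What to change.** In Analysis of effectiveness:

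1. Make one joint Wald or likelihood-ratio test of all arm-by-covariate interactions the test of the secondary hypothesis in each model. Use 0.05 per model, because the two models answer separate questions.
2. Report every individual interaction with its 95 % confidence interval, labelled exploratory.
3. Limit the 0.05 sentence, as far as the effectiveness analysis goes, to the primary test and these two joint tests.

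This takes a few sentences and two tests from models already planned, with no new data. The loss of power when only one characteristic modifies the effect should be stated in the plan. It is the reason to show all individual estimates whatever the joint result.
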